#### Inclusion criteria

Patients fulfilling all the following criteria will be eligible for inclusion in this study:1) Diagnosis of painful bone metastases (multiple metastases are acceptable)2) The most painful bone metastases involve the thoracic spine, lumbar spine, pelvis, or rib(s), for which arterial embolization is expected to relieve pain3) No evidence of spinal cord compression on CT or MRI scan of the most painful bone metastases4) Numerical rating scale (NRS) score of ≥ 5 (Max10) for bone metastatic pain5) Current use of opioid analgesics6) No radiotherapy (RT) at the planned site(s) of TAE within the preceding 3 months7) No initiation of new chemotherapy or hormone therapy within the preceding 2 weeks8) Patients with any cancer9) Life expectancy > 1 month10) Normal renal function and no bleeding risk11) Age ≥ 20 years12) Ability to provide written informed consent to participate in the study

#### Exclusion criteria

Patients fulfilling any of the following criteria will be excluded from this study:1) Inability to remain in the supine position2) Inability to describe pain on an NRS [12, 13]3) History of contrast media allergy4) Inability to discontinue anticoagulants, antithrombotics, or antiplatelet medication other than aspirin5) Childbearing potential6) Inappropriate for enrollment in the opinion of the investigator or sub-investigator

### Intervention for bone metastases

The study treatment will be performed in an angiography suite on an inpatient basis. An angiography device that can be used in digital subtraction angiography (DSA) is necessary. It is desirable that cone beam CT and/or CT angiography are available.

As with conventional angiography, the femoral artery is punctured under local anesthesia to insert an angiographic sheath. Using an imaging catheter (parent catheter: 3 to 5 Fr) from the sheath, a parent vessel of the feeding artery is selected and imaged to localize the tumor and determine the vascular morphology. A microcatheter (1.7 to 2.5 Fr) is then inserted through the parent catheter to select arteries feeding the target lesion. After selecting the feeding arterial branches, angiography is performed to confirm that the relevant region includes abundant tumor stain, but not blood vessels in which embolization is contraindicated. The catheter position is adjusted so that the embolization range does not affect non-target tissues. Spherical embolic material is then slowly injected into the artery to embolize it (Fig. 2). In Japan, spherical embolic material was approved for insurance coverage in 2013, and four products (Embosphere®, BioSphere Medical, Rockland MA, USA), DC Bead® (Biocompatibles UK, Surrey, UK), HepaSphere® (BioSphere), and Embozene® (CeloNova Biosciences, Newnan GA, USA) are commercially available as of 2020.

**Fig. 2 Fig2:**
[figure not shown]
Example of arterial embolization **a**. Lumbar artery: DSA before embolization **b**. Lumbar artery: DSA after embolization

In this study, spherical embolic material will be primarily used to embolize arteries feeding the tumor. Spherical embolic material has been clinically applied since it was commercialized in Europe in the early 1990s. This material is characterized by its reliable embolization of target blood vessels, because it is spherical with uniform diameter and does not aggregate. In this regard, it is unlike conventional gelatin preparations and polyvinyl alcohol (PVA), which are irregular in shape and diameter. It allows embolization of blood vessels of a specific target size with less proximal embolization, and contains fewer proinflammatory raw materials.

### Permitted concomitant therapies

All cancer treatments (including chemotherapy, immunotherapy, and Chinese medicine) that have been used since before enrollment in the study can be continued. Hydroxyzine, pentazocine, opioid analgesics, dexmedetomidine, and midazolam can be used as premedication before TAE. For post-embolization syndrome following arterial embolization, NSAIDs, acetaminophen, rescue opioid analgesics, and adjuvant analgesics can be used for transient exacerbation of pain, and antiemetics can be used for nausea.

### Prohibited concomitant therapies

Subjects may not start any new cancer treatment (including surgery, chemotherapy, molecularly-targeted drugs, therapeutic antibodies, hormone therapy, immunotherapy, Chinese medicine, or radiotherapy) between enrollment in the study and assessment at 2 weeks after arterial embolization.

### Endpoints

#### Efficacy

The primary endpoint (efficacy) is the proportion of subjects with pain relief at 72 h after TAE.

Compared with standard treatments for painful bone metastases, TAE is expected to produce a much more rapid response. Good pain relief may be achieved very rapidly after the start of palliative care by combining current standard treatments with TAE. Therefore, the proportion of subjects with pain relief as early as 72 h post-treatment is selected as the primary endpoint for immediate efficacy.

The assessment method and response assessment will be conducted in accordance with the International Consensus on Palliative Radiotherapy Endpoints, an international consensus proposed for clinical trials of palliative radiotherapy for bone metastases [14]. A responder is defined as a subject with a complete response (CR) or partial response (PR).

### Safety (secondary endpoint)

The secondary endpoint (safety) is the incidence of all CTCAE Grade 4 adverse events and CTCAE Grade ≥ 3 CNS necrosis associated with the arterial embolization procedure.

In this study, the incidence of all CTCAE Grade 4 adverse events and CTCAE Grade ≥ 3 CNS necrosis associated with the arterial embolization procedure will be assessed in the 2-week post-TAE observation period.

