**Methods:**

This study will be a multicenter, single-arm confirmatory study (phase 2–3 design). Patients with painful bone metastases from any primary tumor are eligible for enrollment. TAE will be the main intervention. Following puncture of the femoral artery under local anesthesia and insertion of an angiographic sheath, angiography will confirm that the injected region includes tumor vasculature. Catheter position will be adjusted so that the embolization range does not include non-target tissues. Spherical embolic material will then be slowly injected into the artery to embolize it. The primary endpoint (efficacy) is the proportion of subjects with pain relief at 72 h after TAE and the secondary endpoint (safety) is the incidence of all NCI Common Terminology Criteria for Adverse Events version 5.0 Grade 4 adverse events and Grade ≥ 3 necrosis of the central nervous system.

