### Study setting

This study is a multicenter, single-arm confirmatory study to clarify the efficacy and safety profile of TAE for painful bone metastases (phase 2–3 design).

All participants will be recruited from 24 hospitals: Aichi Medical College, Aichi Cancer Center, Iwate Medical College, Cancer Institute Hospital of JFCR, Tonan Hospital, National Cancer Center Hospital, National Cancer Center Hospital East, Shizuoka Cancer Center, Juntendo Hospital, Teina Keijinkai Hospital, Hokkaido University Hospital, Ryukyu University Hospital, Osaka University, Kobe University, Keio University, Saiseikai Fukuoka Sogo Hospital, Nara City Hospital, Hakodate Goryokaku Hospital, Hyogo Cancer Center, Hyogo Medical University, Fukuchiyama City Hospital, Nara Medical Hospital, St. Marianna University Hospital, and Hokkaido Cancer Center.

The protocol treatment will be performed on inpatients.

To ensure the safety of subjects, registration will be suspended to evaluate safety once 20 subjects are recruited. In the exploratory phase, if any CTCAE Grade 4 adverse event or a Grade 3 or higher adverse event of central nervous system (CNS) necrosis occurs in at least 4 of the 20 subjects, the study will be discontinued (stopping rule) (Fig. 1).

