### Sample size

The clinical hypothesis is that patients with painful bone metastases can be safely treated with arterial embolization for immediate pain relief.

The early response rate after arterial embolization must exceed that after radiotherapy in order for arterial embolization to be established as a new palliative therapy. Since the early response rate was reported to be 26% at 1 week after radiotherapy [16], it is assumed to be lower at 72 h after radiotherapy.

Assuming that the threshold for the proportion of subjects with pain relief at 72 h after arterial embolization, i.e., the primary efficacy endpoint, is 26%, and the expected response rate is 40%, which represents the minimum clinical utility, at least 113 patients are required to provide a power of 90% at a one-sided significance level of 2.5% (normal approximation test).

On the other hand, an adverse event associated with TAE, which is the primary safety endpoint, is defined as any CTCAE Grade 4 adverse event or Grade ≥ 3 CNS necrosis. As described in “Common Adverse Events Associated with Arterial Embolization,” adverse events (including mild events) have been reported in 5% to 7% of patients who undergo arteriography, 10% of patients treated with arterial embolization, and approximately 15% of patients treated with TACE. Considering that patients in poor general condition will be included in this study, the unacceptable threshold incidence for the clinical use of this treatment is set at 15%, equal to that for TACE for hepatocellular carcinoma [17]. Assuming that the incidence will actually be approximately 5% in this study where no anticancer drugs will be used concomitantly; and that bones will be treated, at least 96 patients are required to provide a power of 90% at a one-sided significance level of 2.5% (normal approximation test) (Fig. 1).

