### Statistical methods of analysis

As defined in the Section “Primary Endpoints,” the proportion of subjects with pain relief 72 h after arterial embolization and its two-sided 95% confidence interval (Clopper-Pearson method) will be calculated. It will be determined whether the lower limit of the two-sided 95% confidence interval is > 26%, the threshold response rate established at the time of study design. For reference, the *p*-value will be calculated by a binomial test.

Safety will be evaluated in the Safety Analysis Set (SAS) (Table 2). As defined in “Safety,” the incidence of all CTCAE Grade 4 adverse events and CTCAE Grade ≥ 3 adverse events of CNS necrosis associated with TAE and its two-sided 95% confidence interval (CI) (Clopper-Pearson method) will be calculated. It will be determined whether the upper limit of the two-sided 95% CI is < 15%, the threshold incidence established at the time of study design. For reference, the *p*-value will be calculated by a binomial test.

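### As worded, the safety event counts Grade 4 but not Grade 5, so a procedure-related death other than from CNS necrosis can miss both the 15% criterion and the 4-of-20 stopping rule

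*Protocol article*

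**What the plan says.** The safety event is described in five places in the protocol article, each time with Grade 4 standing alone:

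- Abstract, Methods: "Grade 4 adverse events and Grade ≥ 3 necrosis of the central nervous system".
- Study setting (stopping rule): the rule applies "if any CTCAE Grade 4 adverse event or a Grade 3 or higher adverse event of central nervous system (CNS) necrosis occurs". The boundary is four or more such subjects among the first 20, which ends the study.
- Safety (secondary endpoint): "the incidence of all CTCAE Grade 4 adverse events and CTCAE Grade ≥ 3 CNS necrosis associated with the arterial embolization procedure". The observation window is the two weeks after TAE.
- Sample size: the event "is defined as any CTCAE Grade 4 adverse event or Grade ≥ 3 CNS necrosis".
- Statistical methods of analysis: "the incidence of all CTCAE Grade 4 adverse events and CTCAE Grade ≥ 3 adverse events of CNS necrosis associated with TAE", to be judged by whether the upper limit of the two-sided 95% Clopper-Pearson interval lies below 15%.

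The section on the incidence of adverse events associated with arterial embolization adds a separate secondary endpoint covering all TAE-associated events of Grade ≥ 2. It has no threshold and no stopping consequence. Table 1 defines the safety analysis set, which is the denominator, as all enrolled subjects treated at least once.

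**The concern.** In each of the five places CNS necrosis is written as Grade ≥ 3 or Grade 3 or higher, and the general adverse event endpoint as Grade ≥ 2. The article therefore marks open-ended grades elsewhere, but not for this component. No section mentions Grade 5 or fatal events, or says that Grade 4 is meant to include them.

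Two decisions rest on this event: whether the study is discontinued at 20 subjects, and whether the treatment is declared acceptably safe at the end. There is no control arm, and the Discussion relies on strict thresholds and stopping rules for the reliability of the results. A treated subject who dies from, say, a procedural haemorrhage stays in the denominator. Unless a Grade 4 event was also recorded, that subject adds nothing to the numerator. An analyst who follows the text would score the subject as having no safety event.

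**Working it through.** **Inputs.** From Sample size: unacceptable rate p0 = 15%, expected rate p1 = 5%, one-sided significance level 2.5%, power 90%, N = 96. From Statistical methods of analysis: pass if the Clopper-Pearson 95% upper limit is < 15%. From Study setting: stop at ≥ 4 of 20. From the study schema: 120 subjects planned. Two assumptions are added. A fatal event is graded 5, the usual CTCAE convention, which the article does not spell out. The rates of additional fatal events are assumed because the article gives none.

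**Step 1: reproduce the plan's figure.**

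n = [z(0.975)·√(p0(1−p0)) + z(0.90)·√(p1(1−p1))]² / (p0−p1)²

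= [1.960 × 0.3571 + 1.282 × 0.2179]² / 0.10² = 95.87, rounded up to 96.

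This agrees with the article. The sample size is not in error, and it does not depend on which grades are counted as long as 15% and 5% are kept.

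**Step 2: find the pass limit.** The upper limit for x events in n subjects is the 97.5% quantile of Beta(x+1, n−x).

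| Treated | Most events that pass | Upper limit | Upper limit with one more event |
|---|---|---|---|
| 96 | 7 | 14.4% | 15.8% |
| 113 | 9 | 14.6% | 15.7% |
| 120 | 10 | 14.8% | 15.8% |

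With 120 treated, 10 subjects with Grade 4 events pass. Under the literal wording they still pass with any number of further subjects who die of something other than CNS necrosis and have no recorded Grade 4 event. If such deaths are counted, one of them makes 11 and the criterion fails.

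**Step 3: chance of passing.** Let 5% of subjects have a counted event, and let a further fraction d have an uncounted fatal event and no Grade 4 event. As written, the chance of passing is P(X ≤ limit) with X ~ Binomial(n, 0.05), whatever d is. With deaths counted, X ~ Binomial(n, 0.05 + d).

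| Treated | As written, any d | d = 1% | d = 2% | d = 3% | d = 5% |
|---|---|---|---|---|---|
| 120 | 96.2% | 89.3% | 78.1% | 63.5% | 33.6% |
| 113 | 94.3% | 85.9% | 73.3% | 58.2% | 29.6% |
| 96 | 89.2% | 78.1% | 64.2% | 49.4% | 24.5% |

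**Step 4: the look at 20 subjects.** P(X ≥ 4) with X ~ Binomial(20, p) is 1.6% at p = 5%, 13.3% at 10% and 35.2% at 15%. If the extra 5 or 10 percentage points consist entirely of uncounted fatal events, the chance of stopping stays at 1.6% as written.

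**The case against.** The strongest reply is that Grade 4 is shorthand for Grade 4 or worse. The article condenses a full protocol that is not shown, and it is hard to believe that the investigators meant to count fatal CNS necrosis but not fatal haemorrhage. One phrase carried through five places would explain the consistency. This may well be right about intent, and a reader should not infer that deaths were deliberately excluded. It does not rescue the text, which states the definition in full, attaches two decision rules to it, and nowhere says that higher grades are included.

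Two further readings go beyond the article:

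- **That a death improves the safety rate.** It does not. Such a death leaves the numerator unchanged. The rate would fall only if a Grade 4 event that became fatal were regraded and lost its Grade 4 count, and the article states no such rule. The incidence equation counts subjects with at least one event, so a separately recorded Grade 4 event before death would still count.
- **That deaths go unreported.** They do not. TAE-associated Grade 5 events fall within the Grade ≥ 2 incidence. What they lack there is any bearing on a decision.

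It is also fair to object that the size of the effect is hypothetical. Nothing in the article suggests a particular procedural mortality, so the rates in Step 3 show what the wording permits and do not forecast an effect. Finally, Trial registration reports 36 participants by August 2022, so the look at 20 subjects has probably passed, and rewording the rule cannot change that decision prospectively.

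**Conclusion.** The point holds in a limited form. As worded, a procedure-related Grade 5 event other than CNS necrosis, in a subject with no separately recorded Grade 4 event, counts toward neither the 15% criterion nor the 4-of-20 rule. This is a stated rule that can give a wrong answer, not a detail left to another document.

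The size depends on how many such deaths occur. If there are none, nothing changes. With 120 treated and 5% Grade 4, an assumed extra fatal rate of 1% would lower the chance of passing by about 7 percentage points if deaths were counted (96.2% − 89.3% = 6.9), and an assumed 5% by about 63 (96.2% − 33.6% = 62.6). The literal wording registers neither. These figures assume that fatal events occur in subjects without a Grade 4 event, so that the two rates add. No stated figure in the article is wrong, and nothing in it shows that any such death has occurred.

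**What to change.** - In the abstract, Safety (secondary endpoint), Sample size and Statistical methods of analysis, define the event identically as Grade ≥ 4 (including Grade 5) or Grade ≥ 3 CNS necrosis, keeping the attribution to the procedure.
- Reconcile the event wording of the stopping rule in Study setting with that definition.
- Record the change as an amendment, with its date and a statement that it was made without reference to accumulated outcomes. This matters because the trial is single-arm and unblinded and was already enrolling.
- Recount all subjects already treated, including the first 20, under the clarified definition, and report whether any count changes.

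The cost is a documented amendment during an unblinded trial and possibly a slightly less favourable reported incidence. The safety sample size of 96 stands if 15% and 5% are kept, and no new data need be collected.

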### Secondary endpoints

#### Incidence of adverse events associated with arterial embolization

The incidence of all CTCAE Grade ≥ 2 adverse events associated with TAE will be investigated. Further, arterial embolization for painful bone metastases is not technically difficult and is thus feasible for clinical introduction; given that this may be a key point, the proportion of subjects treated with arterial embolization is included as another secondary endpoint.

The incidence of adverse events will be calculated using the following equation:1$$incidence of adverse events = number of subjects with at least one adverse event/ Safety analysis set (SAS)$$

#### Proportion of subjects treated with TAE

The proportion of subjects treated with arterial embolization will be calculated using the following equation:2$$proportion of subjects treated with arterial embolization = (SAS - subjects discontinued from treatment)/SAS$$

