#### Proportion of subjects with a complete response

To demonstrate that TAE is more effective than placebo, the proportion of complete responders will be assessed.

The proportion of complete responders will be calculated using the following equation:4$$proportion of complete responders = complete response/(FAS - subjects with missing data)$$

The definition of an analysis set is the population of subjects enrolled in the study, excluding those who are doubly or wrongly registered (Table 1).

**Table 1 Tab1:** The definition of each analysis set

Analysis set	Definition
All enrolled subjects	Population of subjects enrolled in the study, excluding those who are doubly or wrongly registered
Full analysis set (FAS)	Population of all enrolled subjects, excluding the following subjects:
	● Subjects who are found ex post facto to be ineligible (fail to meet all of the eligibility criteria or meet any of the exclusion criteria) based on information obtained in accordance with the protocol
	● Subjects who are found to be ineligible based on information obtained after enrollment or unscheduled examination results
	● Subjects who have never received transcatheter arterial embolization (non-implementation)
	● Subjects from whom no data have been collected after enrollment, except information at enrollment into the study
Safety analysis set (SAS)	Population of all enrolled subjects who have been treated with arterial embolization at least once
Per protocol set (PPS)	Population of subjects in the FAS who are in compliance with the protocol

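### Equation 2 takes the proportion treated with TAE among subjects already embolised, so enrolled subjects in whom embolization was not done cannot affect this feasibility endpoint

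*Protocol article*

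**What the plan says.** Under the heading on incidence of adverse events, the protocol article states that embolization for this indication "is not technically difficult and is thus feasible for clinical introduction". Because this may be a key point, it adds the proportion treated as a secondary endpoint. The next section gives equation 2, which reads ("SAS - subjects discontinued from treatment)/SAS".

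Table 1 defines three sets that matter here:

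- SAS: "Population of all enrolled subjects who have been treated with arterial embolization at least once".
- All enrolled subjects: the "population of subjects enrolled in the study, excluding those who are doubly or wrongly registered".
- Full analysis set (FAS): among its exclusions are "Subjects who have never received transcatheter arterial embolization (non-implementation").

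The section on the intervention puts femoral puncture, catheterisation and angiography before any embolic material is injected. Once the feeding branches are selected, "angiography is performed to confirm that the relevant region includes abundant tumor stain, but not blood vessels in which embolization is contraindicated".

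The SAS is also the denominator for adverse-event incidence (equation 1) and the population for the 15% safety test (Statistical methods of analysis).

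**The concern.** An endpoint offered as evidence that the technique is feasible should fall when the technique cannot be carried out. Equation 2 starts from subjects in whom it has already been carried out at least once. A subject whose feeding artery cannot be selected, or whose angiogram shows a vessel that must not be embolised, never enters the SAS and so cannot count as a failure. Such a subject is not far-fetched: Table 1 names non-implementation as a category, and the angiographic check before injection is one way it can arise.

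At stake is a published feasibility figure that would stay close to 100% however many enrolled subjects could not be embolised.

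The same definition has a smaller consequence for safety. Subjects who were punctured and catheterised but not embolised fall outside the set in which adverse events are counted.

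**Working it through.** **The plan's own figures.** The article gives no expected value for the feasibility endpoint, so there is none to reproduce. Its two sample sizes do reproduce with n = [(z₀.₉₇₅√(p₀(1−p₀)) + z₀.₉₀√(p₁(1−p₁)))/(p₁−p₀)]²:

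- Efficacy, 26% against 40%: 112.90, rounded up to 113.
- Safety, 15% against 5%: 95.87, rounded up to 96.

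Neither depends on equation 2.

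**Feasibility: inputs.** N = 120 planned (Fig. 1 legend). Let k be the enrolled subjects never embolised and d the subjects discontinued after embolization had begun. The article gives neither, so both are assumptions. By Table 1, SAS = N − k.

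- Equation 2: (N − k − d)/(N − k)
- Over all enrolled: (N − k − d)/N

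With d = 0, equation 2 is (N − k)/(N − k) = 100% for every k. Limits below are Clopper-Pearson 95%.

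| k | Equation 2 | Over all enrolled |
|---|---|---|
| 5 | 115/115 = 100% | 115/120 = 95.8% (90.5 to 98.6) |
| 10 | 110/110 = 100% | 110/120 = 91.7% (85.2 to 95.9) |
| 15 | 105/105 = 100% | 105/120 = 87.5% (80.2 to 92.8) |

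With d = 2, as k goes from 0 to 24, equation 2 moves only from 118/120 = 98.3% to 94/96 = 97.9%. The all-enrolled figure falls from 118/120 = 98.3% to 94/120 = 78.3%.

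**Could the subtracted term cover never-embolised subjects?** They are not in the SAS, so they cannot be subtracted from it. If they were subtracted anyway, k = 10 would give (110 − 10)/110 = 90.9%. That counts ten embolised subjects as untreated and is not the 91.7% wanted.

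**Safety: effect of the set on the 15% test.** The rule is that the Clopper-Pearson upper limit, the 97.5% quantile of Beta(x + 1, n − x), must be below 15%. Assume 114 embolised and 6 punctured but not embolised.

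| Events in SAS | Events in the other 6 | SAS upper limit | All 120 upper limit |
|---|---|---|---|
| 9 | 2 | 9/114: 14.46%, passes | 11/120: 15.81%, fails |
| 9 | 1 | 9/114: 14.46%, passes | 10/120: 14.79%, passes |
| 10 | 0 | 10/114: 15.54%, fails | 10/120: 14.79%, passes |

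Widening the set can turn a pass into a fail, leave the result alone, or turn a fail into a pass.

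**The case against.** The best defence of equation 2 is that discontinuation is not defined in this condensed article, and that the intervention section treats the whole session as the study treatment. If being treated meant that a procedure had been started, equation 2 would be a completion rate among started procedures, which is a reasonable technical measure. Table 1 tells against this. The SAS requires embolization at least once, and the FAS exclusion for non-implementation is worded as never having received it. The part that stands is that a procedure stopped after some embolic has been given can lower equation 2, so it is not fixed at exactly 100%.

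A second objection is that the stated purpose concerns technical difficulty, whereas an all-enrolled denominator also counts subjects who withdrew or deteriorated before reaching the angiography suite. That is fair, and it is why a second proportion among started procedures is needed.

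A reader might also infer that the safety test uses the wrong population and that the SAS should be redefined from arterial puncture. The documents do not support this:

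- A set of subjects treated at least once is conventional for safety.
- The arteriography risk cited in the sample size section ("adverse events (including mild events) have been reported in 5% to 7% of patients who undergo arteriography") includes mild events, whereas the tested endpoint is Grade 4 events or Grade ≥ 3 CNS necrosis.
- Observation is timed from embolization for two weeks, and nothing shows that unembolised subjects are followed for that long.
- Adding event-free subjects who received no embolic can loosen the test, as the last row of the safety table shows.

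**Conclusion.** The point on equation 2 holds on the printed definitions: the endpoint does not respond to non-implementation. The size of the error depends on how many subjects are not embolised, which the article does not state. With 5, 10 or 15 of 120 and no discontinuations, the overstatement is 4.2, 8.3 or 12.5 percentage points (100 minus 95.8, 91.7 or 87.5).

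It would be too strong to say that the trial cannot answer its feasibility question. Never-embolised subjects must be identified to form the FAS, so they can be counted. Only the printed formula leaves them out. The endpoint is secondary, with no threshold or test attached, and the 72-hour efficacy analysis does not use it.

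On safety, what is supported is an added analysis and not a new test population. How far subjects punctured but not embolised would change the incidence is unknown and may be small.

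**What to change.** 1. Restate equation 2: numerator, subjects with embolization completed; denominator, all enrolled subjects (Table 1, row 1).
2. Report the same numerator over subjects in whom the procedure was started (arterial puncture), to separate technical failure from withdrawal before the procedure.
3. Define completed embolization and discontinuation from treatment, so that each enrolled subject falls in one category.
4. Keep the SAS for the 15% test. Add a sensitivity analysis of the same incidence, with a listing of events, in all subjects in whom the procedure was started.

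The cost is a change of definitions, a less favourable feasibility figure and one extra analysis. The extra analysis depends on adverse events being recorded for subjects who were punctured but not embolised. The article does not show that they are, and 36 patients had already taken part by August 2022, so this should be checked for them as well. The sample sizes do not change.
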